### Enrollment and allocation

Participants were randomly assigned in a 1:1 ratio to either the HBP-AMRI arm or the US arm using a permuted block randomization method with a random block size of 4. Allocation concealment was ensured through the use of a sequestered code, accessed only after informed consent was obtained. The study is open-label, as both participants and investigators were aware of the surveillance assignment due to the visible procedural differences between US and HBP-AMRI.

### Participant flow

A trained research coordinator introduced the trial to potentially eligible patients during outpatient clinic visits or scheduled assessments. Patients who met all eligibility criteria received comprehensive verbal and written information about the study’s objectives, procedures, risks, and potential benefits. Adequate time was provided for consideration, and informed discussions with investigators were encouraged. Written informed consent was obtained from those who agreed to participate.

Upon enrollment, participants were randomly assigned in a 1:1 ratio to undergo 2 consecutive rounds of HCC surveillance using either biannual US or biannual HBP-AMRI at 6-month intervals (with a variation of ±1 mo allowed) (Figure 1). The first surveillance test is scheduled for ~6 months after the participant’s last imaging study, confirming the absence of hepatic malignancy.

**FIGURE 1 F1:**
[figure not shown]
Participant flow. Abbreviations: HBP-AMRI, hepatobiliary phase-abbreviated magnetic resonance imaging; LR, Liver Imaging Reporting and Data System category; US, ultrasonography.

If a lesion is detected and considered potentially malignant based on predefined radiologic criteria (see *Imaging Evaluation* section below), a confirmatory imaging test will be conducted. Participants with no suspicious findings will proceed to the second surveillance round at the scheduled interval. Following completion of the second surveillance round, all participants will enter a 6-month observation period, during which delayed HCC diagnosis and clinical outcomes will be assessed. If a “positive” lesion is ultimately determined to be a false-positive following the confirmatory test, the participant will return to their assigned surveillance schedule.

Dropout will be defined as: (1) withdrawal of consent or determination by the investigators that the participant is unable to adhere to the protocol; (2) liver transplantation without prior HCC diagnosis, (3) diagnosis of extrahepatic malignancy during the study period, or (4) failure to complete one or more consecutive scheduled surveillance visits. To minimize dropouts, participants will receive up to 2 reminders per visit (3 d and 1 d in advance) via phone call or text message. In addition, staff will offer flexible scheduling support and follow-up if participants miss or need to reschedule an appointment.

Peripheral blood samples will be collected at the screening visit and at each surveillance visit for all enrolled participants following approved protocols. Serum levels of alpha-fetoprotein and protein induced by vitamin K absence-II will be measured at each visit. Stored samples may be used in future ancillary studies. Written informed consent will be obtained from all enrolled participants for specimen collection and future use.

### Ultrasonography

Abdominal US will be performed using a commercially available scanner (Aplio i800, Canon Medical Systems, Otawara, Japan) equipped with a 5-MHz curved-array transducer. All surveillance US examinations will be conducted at Asan Medical Center by board-certified abdominal radiologists. US will be performed following a standardized acquisition protocol recommended by US LI-RADS v2017^27^ and LI-RADS US Surveillance v2024.^28^ Images will be digitally archived for quality assurance and secondary review.

### Abbreviated MRI (HBP-AMRI)

HBP-AMRI will be conducted using 3.0-T scanners available at the study site, including Achieva and Ingenia (Philips Healthcare, Best, the Netherlands), Skyra and Vida (Siemens Healthcare, Erlangen, Germany), and Architect and Premier (GE Healthcare, Milwaukee, WI, USA). All participants will receive a gadoxetic acid injection (Gd-EOB-DTPA, Primovist, Bayer Schering Pharma) at a dose of 0.025 mmol/kg, followed by a 20-mL saline flush in the preparation room. After a 15–20-minute delay, participants will move into the MRI suite for scanning. The protocol will include the following axial sequences: (1) heavily T2-weighted imaging (repetition time, 1100 ms; echo time, 150 ms; slice thickness, 5 mm); (2) respiratory-triggered or free-breathing diffusion-weighted imaging with b-values of 50, 500, and 900 s/mm^2^ (repetition time, 2000 ms; echo time, 54–56 ms; slice thickness, 5 mm) with ADC map reconstruction; and (3) fat-suppressed 3D gradient-echo T1-weighted imaging during HBP using manufacturer-specific sequences [eg, VIBE (Siemens), LAVA (GE), or THRIVE (Philips)] (repetition time, 3.4 ms; echo time, 1.3 ms; slice thickness, 3 mm). Scan time for HBP-AMRI is expected to be under 15 minutes, depending on equipment and patient cooperation.

### Imaging evaluation

All surveillance imaging studies will be interpreted by board-certified abdominal radiologists using a standardized 3-point scale reflecting the likelihood of HCC: positive, subthreshold, and negative (Table 1). Participants with a “positive” result on either modality will undergo confirmatory testing, while those with a “subthreshold” or “negative” result will proceed to the next scheduled surveillance in 6 months.

**TABLE 1 T1:** Lesion categorization on HBP-AMRI and US

Category	HBP-AMRI	US
	Definition	Definition
Positive	▪ A new solid nodule ≥10 mm is not definitely benign^a^ ▪ Changes in imaging characteristics^b^ or threshold growth^c^ of a previous subthreshold observation ▪ New thrombus in the vein	• A new solid nodule or parenchymal distortion ≥10 mm distinct from the background liver • Threshold growth^c^ of previous subthreshold observation • New thrombus in the vein
Subthreshold	▪ Solid nodule <10 mm, not definitely benign^a^ ▪ Previous positive observation confirmed as a false positive	• Solid nodule or parenchymal distortion <10 mm • Previous positive observation confirmed as a false positive
Negative	▪ No observation ▪ Only definitely benign observation^d^	• No observation • Only definitely benign observation^d^

^a^
Mild to moderate hyperintensity on T2-weighted imaging, diffusion restriction, or hypointensity on hepatobiliary-phase imaging.

^b^
Any new appearance of not definitely benign characteristics.

^c^
Size increase by ≥50% in ≤6 months.

^d^
Cyst, hemangioma, or other previously characterized benign lesion.

Abbreviations: HBP-AMRI, hepatobiliary phase-abbreviated magnetic resonance imaging; US, ultrasonography.

For HBP-AMRI, a “positive” result is defined as the presence of a new solid nodule ≥10 mm that does not demonstrate definitely benign characteristics (mild to moderate hyperintensity on T2-weighted imaging, diffusion restriction on diffusion-weighted imaging, or hypointensity on HBP imaging), changes in imaging characteristics or threshold growth of a previous subthreshold observation, or development of new thrombus in vein (TIV). Benign entities such as cysts, hemangiomas, and previously characterized benign lesions are not considered positive, regardless of size.

For US, classification follows the criteria of US LI-RADS v2017^27^ and LI-RADS US Surveillance v2024.^28^ A “positive” result is defined as a new solid nodule or parenchymal distortion ≥10 mm that is distinct from the background liver, threshold growth of a previous subthreshold observation, or new TIV. Cysts, hemangiomas, or previously characterized benign lesions are not considered positive findings regardless of size. For both HBP-AMRI and US, image quality will be classified as A (no or minimal limitation), B (moderate limitation), or C (severe limitation), as previously described^19^,^28^ (Table 2).

**TABLE 2 T2:** Classification of image quality

Score	HBP-AMRI	US
A (no or minimal limitation)	▪ Liver signal on HBP is considerably higher than that of the vessels ▪ Liver texture: homogeneous or mildly heterogeneous	▪ Liver is homogeneous or minimally heterogeneous ▪ Minimal beam attenuation or shadowing ▪ Liver visualized in near entirety
B (moderate limitation)	▪ Liver signal on HBP is only slightly higher than that of the vessels ▪ Liver texture is moderately heterogeneous	▪ Liver moderately heterogeneous ▪ Moderate beam attenuation or shadowing ▪ Some portion of the liver or diaphragm is not visualized
C (severe limitation)	▪ Liver signal on HBP is the same or lower than that of the vessels ▪ Liver texture is severely heterogeneous ▪ Severe artifact	▪ Liver severely heterogeneous ▪ Severe beam attenuation or shadowing ▪ The majority (>50%) of the liver or diaphragm is not visualized

Abbreviations: HBP, hepatobiliary phase; HBP-AMRI, hepatobiliary phase-abbreviated magnetic resonance imaging; US, ultrasonography.

### Reference standards

The reference standard for final diagnosis will begin with radiologic confirmation using a complete dynamic contrast-enhanced MRI with an extracellular contrast agent (Dotarem; gadoterate meglumine; Guerbet, Roissy, France), interpreted according to CT/MRI LI-RADS v2018.^29^ Lesions classified as LR-5 will be considered diagnostic of HCC. For lesions classified as LR-4, LR-M, or LR-TIV, additional imaging evaluation—including liver dynamic CT, dynamic contrast-enhanced MRI with gadoxetic acid, or contrast-enhanced US or histologic confirmation via US-guided biopsy—will be performed based on multidisciplinary discussion.

For lesions classified as LR-3, if the lesion is pre-existing without interval change, the participant will return to the study and undergo subsequent surveillance testing. If the LR-3 lesion is newly identified or shows any change in image characteristics (ie, new appearance of mild to moderate T2 hyperintensity, diffusion restriction, or hypointensity on HBP imaging), follow-up imaging will be performed within 3–6 months. Participants with the lesion classified as LR-1 or LR-2 will return to the study and undergo subsequent surveillance testing.

### Outcomes

The primary endpoint of this trial is the detection rate of early-stage HCC, defined as Barcelona Clinic Liver Cancer (BCLC) stage 0 or A.^30^ Detection rate is defined as the number of patients whose BCLC 0 or A HCC is detected using a given surveillance modality, divided by the total number of patients under surveillance with that modality, expressed as a percentage. Secondary endpoints include the false referral rate of BCLC 0 or A HCC, detection and false referral rates of BCLC stage 0 HCC, detection and false referral rates of all-stage HCC, distribution of BCLC stages at initial HCC diagnosis, and the rate at which curative treatment (surgical resection and local ablative therapies including radiofrequency ablation, microwave ablation, and cryoablation) is received. False referral rate is defined on a per-exam basis, calculated as the number of surveillance tests interpreted as positive but subsequently confirmed as non-malignant on confirmatory examination, divided by the total number of surveillance tests performed in that modality arm, expressed as a percentage.

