#### Exclusion criteria

Presence of an active or suspected cancer, or a history of treated malignancy with a risk of recurrence ≥20% within 2 years.Significant comorbidity with an expected survival of <3 years.Estimated glomerular filtration rate <30 mL/min/1.73 m^2^.Child–Pugh class C.Conditions precluding application of the Liver Imaging Reporting and Data System (LI-RADS) (eg, Budd–Chiari syndrome or other hepatic vascular disorders).Contraindications to MRI (eg, pacemakers, severe claustrophobia, pregnancy).Any condition deemed by the investigators to interfere with study participation or protocol adherence.

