### Sample size

The sample size was calculated based on a 2-sided test for comparing 2 independent proportions, with the primary endpoint being the detection rate of early-stage HCC. Based on prior prospective studies in real-world surveillance settings,^12^,^13^,^14^ we assumed a cumulative prevalence of very early or early-stage HCC of 8% during the study period. The sensitivity of HBP-AMRI was estimated at 90%, and that of US at 35%, reflecting the range observed in surveillance cohorts of patients with cirrhosis.^12^,^13^,^14^ Accordingly, we assumed detection rates of 7.2% for HBP-AMRI and 2.8% for US. To detect a statistically significant difference in detection rates between the 2 modalities, with 80% power and a 2-sided alpha of 0.05, and accounting for an anticipated 5% dropout rate, the total required sample size is 806 participants (403 per arm).

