### Statistical analysis

Detection rates and the rate of curative treatment will be compared using the Fisher exact test. BCLC stage distribution will be compared using the chi-square test. False referral rates will be compared using Fisher exact test or Poisson regression analysis. Time to tumor detection will be analyzed using Kaplan–Meier methods and compared using the log-rank test. Associations between liver function as assessed by Child–Pugh (ie, Child–Pugh A or B), and surveillance image quality, as well as between image quality and detection or false referral rates, will be examined using chi-square or Fisher exact tests as appropriate. If appropriate, multivariable logistic regression analyses will be used to determine the independent associations between variables. All tests will be 2-sided, with *p*-values <0.05 considered statistically significant. Statistical analyses will be conducted using SAS version 9.2 (SAS Institute Inc., Cary, NC, USA).

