## DISCUSSION

The aim of the AMRIUS trial is to determine whether surveillance using HBP-AMRI with gadoxetic acid improves early HCC detection performance in high-risk patients with cirrhosis compared with conventional US. We are employing a 2-arm randomized design to enable a direct comparison of the 2 imaging modalities while minimizing bias, thereby providing robust evidence to evaluate the potential superiority of HBP-AMRI over US.

Early detection of HCC plays a pivotal role in surveillance, as curative treatments such as surgical resection and ablation are feasible when HCCs are identified at an early stage, typically BCLC stage 0 or A. To align with this clinically meaningful goal, we defined the primary endpoint as the detection rate of BCLC stage 0 or A HCC. In addition, the false referral rate, included as a key second endpoint, captures the broader impact of surveillance by reflecting unnecessary diagnostic procedures, patient anxiety, and healthcare resource consumption.^31^,^32^,^33^ Furthermore, by investigating the initial stage distribution of detected HCCs, we intend to assess the extent to which each surveillance modality enables detection at a stage amenable to curative treatment.

Among at-risk individuals, the likelihood of HCC varies according to underlying etiology (eg, viral hepatitis, alcohol-associated liver disease, or metabolic dysfunction–associated steatotic liver disease), degree of liver fibrosis, and other clinical parameters. As such, a uniform surveillance strategy may not be optimal, and recent guidelines and expert recommendations increasingly support risk-stratified surveillance tailored to individual patient profiles.^33^ By enrolling patients with a quantitatively defined high risk for HCC (estimated annual risk >5%), the AMRIUS trial is positioned to contribute evidence toward this evolving strategy. Its findings may help identify subgroups that derive the greatest benefit from high-sensitivity modalities such as HBP-AMRI and also provide evidence on the most suitable surveillance modality for these populations, thereby supporting the future development of personalized surveillance strategies.

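### The curative-treatment endpoint lists only resection and ablation, so read literally a participant transplanted for a diagnosed HCC counts as not curatively treated

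*Protocol article*

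**What the plan says.** Three places in the protocol article bear on this.

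- **Outcomes.** The secondary endpoint is the rate at which "curative treatment (surgical resection and local ablative therapies including radiofrequency ablation, microwave ablation, and cryoablation) is received". The bracket has two members, resection and local ablation. The word introducing the three techniques attaches to ablation and does not open the list to other treatments.
- **Participant flow, dropout definition.** The only mention of transplantation in the article is the second dropout criterion, "liver transplantation without prior HCC diagnosis". A transplant after an HCC diagnosis does not meet it.
- **Statistical analysis.** "Detection rates and the rate of curative treatment will be compared using the Fisher exact test". No denominator is given for the curative-treatment rate. The article defines the detection rate per patient under surveillance and the false referral rate per examination, but does not say whether this rate is per randomised patient or per patient with HCC.

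The Discussion speaks more loosely: "curative treatments such as surgical resection and ablation are feasible when HCCs are identified at an early stage". That wording is illustrative and does not amend the definition in Outcomes.

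**The concern.** The endpoint is meant to show whether finding tumours earlier leads to treatment with curative intent. All participants have cirrhosis, and the exclusion of "Child–Pugh class C" leaves classes A and B, so transplantation is a foreseeable event. The dropout criterion shows that the authors had it in mind and tied its handling to whether HCC had been diagnosed.

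The two rules do not fit together well. The dropout rule keeps a participant transplanted for HCC in the trial, but the endpoint definition offers no category in which that treatment counts. Such a participant would be grouped with those who received no curative treatment. What is at stake is the level of one secondary rate and the interpretation of its comparison between arms.

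**Working it through.** **1. Following one participant through the rules.** A participant is diagnosed with HCC and then transplanted, without resection or ablation.

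- Dropout criterion 2 does not apply, because HCC was diagnosed first.
- Criterion 4 (missed surveillance visits) cannot sensibly be meant to catch this participant. If it did, it would also remove anyone resected or ablated after the first round.
- The participant is therefore analysed, has neither listed treatment, and is scored as not curatively treated.

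A participant who had ablation or resection as well as a transplant already counts. Only those whose sole treatment of this kind is transplantation are affected.

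**2. The plan's own figure.** Sample size states "we assumed detection rates of 7.2% for HBP-AMRI and 2.8% for US", "with 80% power and a 2-sided alpha of 0.05" and "accounting for an anticipated 5% dropout rate". With the unpooled normal formula:

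- n = (1.96 + 0.8416)² × (0.072 × 0.928 + 0.028 × 0.972) / 0.044² = 7.849 × 0.094032 / 0.001936 = 381.2, rounded up to 382 per arm
- 382 / 0.95 = 402.1, rounded up to 403 per arm, 806 in total

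This reproduces the stated 806. It rests on detection rates alone, so the definition of curative treatment does not enter it.

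**3. Effect on the curative-treatment rate.** In one arm, let c be the number with resection or ablation, t the number treated by transplantation only after an HCC diagnosis, and N the denominator.

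- Rate as written: c/N
- Rate with transplants counted: (c + t)/N
- Shortfall: t/N, which is never negative, so the rate can only be understated

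Per affected patient (t = 1):

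| Denominator | N per arm | Shortfall |
|---|---|---|
| All randomised | 403 | 1/403 = 0.25 points |
| Early-stage HCCs at the assumed 8% prevalence | 403 × 0.08 = 32.2 | 1/32.2 = 3.1 points |

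If the denominator were HCC of all stages, N would exceed 32 and the shortfall per patient would be smaller than 3.1 points. The article gives no all-stage figure.

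**4. Range for the unknown number of transplants.** The article gives no share. The shares below are assumptions, applied to 32.2 early-stage HCCs in an arm.

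| Assumed share transplanted only | Patients per arm | Shortfall, N = 403 | Shortfall, N = 32.2 |
|---|---|---|---|
| 0% | 0 | 0 | 0 |
| 5% | 1.6 | 0.4 points | 5 points |
| 10% | 3.2 | 0.8 points | 10 points |
| 20% | 6.4 | 1.6 points | 20 points |

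**5. Between arms.** The change in the difference (HBP-AMRI minus US) is t/N in the HBP-AMRI arm minus t/N in the US arm. Neither t nor N is given for either arm, so its sign and size are both open.

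**The case against.** **A restricted endpoint can be a legitimate choice.** Resection and ablation are named explicitly, the rule applies equally to both arms, and Outcomes and Discussion name the same two treatments. No passage calls transplantation curative. This stands in part: the two sections do not contradict each other, and treating transplantation for HCC as curative is a general clinical premise brought to the text. But the endpoint is labelled curative treatment without restriction, and nothing says that transplants were left out on purpose.

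**The dropout rule is only a dropout rule.** A reader might infer that the protocol expects transplants after HCC, or states that they are scored as failures. It does neither. The scoring follows from a closed list combined with a dropout criterion that does not apply, and the number of such patients could be zero.

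**The full protocol may cover it.** The article is condensed, and coding of rarer treatments could sit elsewhere. That carries little weight here, since the article gives the definition down to the type of ablation.

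**Stronger readings to resist.**

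- A reader might divide by the early-stage HCCs that each modality is expected to detect: 403 × 7.2% = 29.0 and 403 × 2.8% = 11.3. One transplant would then move the rate by 3.4 points in the HBP-AMRI arm and 8.9 in the US arm. The article does not restrict the denominator to modality-detected cases. The planning prevalence is 8% in both arms, and a 6-month observation period is there to capture delayed diagnoses.
- A reader might conclude that the arm comparison is biased. The same rule applies to both arms, and nothing in the article shows how transplantation after HCC would be distributed between them.

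**Conclusion.** The point holds as a minor correction to one secondary endpoint. Taken together, the endpoint definition and the dropout rule score a participant transplanted for a diagnosed HCC as not curatively treated, and this understates the rate in whichever arm it occurs. The cost per affected patient is about 0.25 points on all 403 randomised per arm, or about 3 points on the roughly 32 early-stage HCCs per arm that the 8% prevalence implies. The total effect, and any effect on the difference between arms, cannot be computed from the article.

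The conclusion rests on reading the bracketed list as complete and on regarding transplantation for HCC as treatment with curative intent. The primary endpoint, the sample size and the other secondary endpoints are not affected.

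**What to change.** In the Outcomes definition, state that liver transplantation performed for a diagnosed HCC counts as curative treatment for classification purposes. This mirrors the dropout criterion, which already separates transplants by whether HCC was diagnosed first. Report the rate limited to resection and ablation as a sensitivity analysis, so that the rate as now defined remains visible. State the denominator of the rate in the same sentence.

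The cost is a phrase in the definition and one additional table row. Under the article's own ethics section a protocol modification needs Institutional Review Board approval. Follow-up is described as ongoing, so the rule can be fixed before analysis. The data section mentions only relevant clinical, imaging and laboratory data, so the sponsor should confirm that the case report form captures transplantation and its timing relative to HCC diagnosis. The change concerns how an outcome is counted and has no bearing on which treatment any participant receives.
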